### Components of the PEGASO platform

The PEGASO system includes physical activity monitoring devices, a web portal, and up to six apps: Companion app, Challenges app, EDiary app, Dashboard app, serious game and Report app.

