#### Companion app

The objective of the Companion app is to encompass all other PEGASO apps (Fig. 2). The Companion App aims to act as a personal digital friend which coaches, cares, and empowers participants in developing healthy habits. It aims to provide the participant with a dynamic stream of educational and motivational messages and updates about their achievements and their friends’ shared achievements. Data acquired via physical activity monitors is presented to the participant via a specific interface presented within the Companion app. The Companion app also includes a reward system and the gamification module to allow the participants to: a) achieve one time rewards (e.g., FitCoins, badges, experience points) for the selected target behaviour and b) achieve cyclic events.

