### Procedures

Eligible participants are introduced to the PEGASO system after they and their parents/guardian provided written and signed consent, and after baseline measurements are collected. Participants are provided with a smart phone (running as OS Android, version from 4.4 to 6.0) with the PEGASO apps installed for the duration of the study.

Given the complexity of the PEGASO system, the components are introduced in two sessions within the same first week. The physical activity monitors are introduced to the participants at the mid-point assessment time at month 4 of the study. This time point was chosen to reduce the burden on the schools and participants, allocating time and resources in addition to the baseline measures, mid-point and follow-up assessment contact points, whilst additionally avoiding conflict with exam timetables and extended holiday periods (e.g. summer break). In addition to familiarising the participants with the functionalities and use of the garment and activity monitors, researchers assist participants in connecting the activity monitors with individual smart phones. All introduction sessions across the four study sites provide a mixture of interactive workshops, educational games, and replicate the method as much as possible within the constraints of the school requirements in different countries.

Participants are offered support during the study to facilitate understanding of how to use the PEGASO system and to trouble-shoot any issues arising. Participants are invited to join a site specific Google Hangout group to allow timely communication with the field researchers who provide solutions to technical issues whenever possible. Teachers at schools are offered a brief training session to be able to answer simple questions related to the use of the PEGASO system. They are asked to direct the participants to the web portal and the FAQ link for questions they cannot answer.

The role of teachers is to support students over the testing period, and to facilitate the communication flow among field researchers, parents and teenagers. During on-site contact points an interaction with teachers is expected; they will have the opportunity to indicate to the field researchers any comments, doubts or conflicts including maladaptive behaviours.

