### Outcomes and variables

The first block of outcomes that will be assessed are related to recruitment and adherence to the intervention, namely recruitment rate, study retention, adherence to the intervention and attitudes to the different components of the intervention.

We aim to test a range of outcomes related to individual lifestyle (dietary habits, physical activity, sedentary behaviour, and sleeping habits), knowledge/awareness about these health habits and user experience of the platform. Individual lifestyle and knowledge/awareness about health habits are assessed at baseline and at the end (6 months) of the intervention both in the comparison and intervention group. User experience is assessed at month 2, 4 and 6 only in the intervention group. Outcomes, instruments and assessment points during the study are detailed in Table 3.

**Table 3 Tab3:** Outcomes, instruments and assessment points in the PEGASO study

Outcome	Instrument	Assessment point			
		BL	M2	M4	M6
Dietary habits	Mediterranean Diet Quality Index in children and adolescents (KIDMED questionnaire) + 5 additional questions	X			X
Physical activity	Physical Activity Questionnaire for Adolescents (PAQ-A) + 3 additional questionnaires	X			X
Sedentary behaviour	Screen time-based sedentary behavior questionnaire (SSBQ)	X			X
Sleeping habits	Sleep Habits Survey (SHS)	X			X
Knowledge questionnaire	Ad hoc questionnaire	X			X
Anthropometric Measurements		X			X
Height	Stadiometer SECA 213	X			X
WC	Flexible graduated measuring tape (SECA 201)	X			X
Weight	*England, Catalonia, Italy*: Homologated	X			X
BMI	electronic scale Tanita SC240MA				
% of body fat	*Scotland*: Tanita MC780MA Multi	X			X
% of body water	Frequency Segmental Body Composition Analyser	X			X
Family affluence and self-reported health status	Family Affluence Scale (FAS) + 1 question from the Social Functioning subscale −12 (SF-12)	X			
*Motivation*	*Perceived Competence Scale*	*X*	*X*	*X*	*X*
*Usability*	*System Usability Scale*			*X*	*X*
*Emotional Response to the Platform*	*Emotional Metric Outcome questionnaire*			*X*	*X*
*Satisfaction, Trust, Reputation*	Ad hoc *questionnaire*			*X*	*X*
*User Experience*	*Focus Groups*			*X*	*X*

In italics, outcomes assessd only in the intervention group. All the other outcomes were assessed in both, intervention and comparative group

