Motivation to maintain or increase healthy dietary habits and physical activity will be assessed through the “Perceived Competence Scale” a short 4-item scale that assesses the degree to which participants feel confident about being able to make (or maintain) a change toward a healthy behaviour [40]. Adolescents’ age, gender, perceived health status level and family affluence will be included in the on-line questionnaires. Parent’s (or legal guardian’s) educational level, occupation and familiar structure will be also documented only at baseline.

User experience (UX) refers to a person’s total experience using a particular product, system or service [41]. The factors of UX to be investigated during the study include: emotion, engagement, trust, reputation, pleasure/hedonism, usability, acceptability, accessibility, connectedness, context and target behaviours adherence. The PEGASO study aims to holistically assess how the teenagers experience the system in their everyday lives and where and how this experience facilitates use and where it can be improved. Mixed methods (quantitative and qualitative methodology) will be used to assess UX, specifically through self-reported questionnaires and focus groups or semi-structured interviews, respectively. The System Usability Scale (SUS) is a well established 10 item questionnaire with five response options to assess usability of a variety of products and services, where usability is a distinct concept within the overall understanding of UX [42]. SUS will be applied at month 4 to assess usability of the Companion and the game and at month 6 for the whole system. The Emotional Metric Outcome (EMO) questionnaire is a 16 item questionnaire to assess the emotional outcomes of interaction, both positive and negative [43]. The EMO will be undertaken at month 4 and 6. A questionnaire has been created ad hoc in order to measure the satisfaction, trust and reputation of the platform. This comprises a 28 item questionnaire with 5 answer categories and is undertaken at months 4 and 6.

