### Focus groups

Key contributors to understanding the UX of the PEGASO system such as; usability, acceptability, accessibility, context of use, connectedness, desirability and pleasure will also be assessed through focus groups; moreover they will be used to gain insight on users understanding of the system and their experience and motivation to engage/disengage with the PEGASO system and its different component parts (apps, games and sensors). Participants in the focus groups will be recruited from participants in the intervention group. A total of four focus groups per participating site (England, Lombardy and Catalonia) will be undertaken at month 4 and 6. Participants in focus groups at month 4 will have only tested the apps and the game of Pegaso, whilst participants on the Month 6 focus groups additionally will have used the sensors for 2 months. Each focus group will consist of 4–8 participants. The groups, whenever possible, will be gender-balanced with different levels of engagement to the PEGASO system. A trained moderator will guide the focus group following a script and will be assisted by an observer. All of them will be audio and/or videotaped and transcribed systematically, literally, and anonymously. An analysis will be made of thematic content, coding the data and grouping them into predefined categories based on topics.

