### Analysis plan and statistical analysis

The analysis plan will include a description of all data at every assessment point and an overall comparison of baseline characteristics between intervention group (IG) and comparison group (CG), as well as by sites and gender. Knowledge/awareness, lifestyles and anthropometric measurements will be compared at pre and post intervention (month 6) utilising an intention-to-treat (ITT) approach, independently from drop-outs and non-adherence. Relevant changes among lifestyles and knowledge will be defined according to current recommendations from international guidelines [46]. The effect of the intervention could be modified by gender, cultural and socioeconomic level, body mass index (BMI), as well as by the baseline lifestyles, which will be controlled in the analysis. Changes in motivation will be assessed in the four assessment points and compared to baseline. For the intervention group, the results from SUS, EMO, satisfaction, trust and reputation questionnaires will be compared from month 4 to month 6. The level of engagement in the PEGASO platform will be assessed from indicators of usage at individual level, such as the number of days of interactions with the APPs or the daily number of steps, stored in the cloud.

Results will be reported as mean ± standard deviation (or median, percentile 25 and 75) for quantitative variables or frequency and percentage distribution for qualitative variables. Quantitative variables will be tested for normality, log-transformed if needed, and accordingly analysed with parametric or non-parametric methods. Chi-squared test will be used to analyse the association between independent qualitative variables, along with the McNemar test for paired samples. The Student t-test will be used for the comparison of means between two groups, and the paired t-test will be applied to assess changes within one same group. Alternatively, the corresponding nonparametric tests will be used, as required. The relationship between quantitative variables will be analysed using Pearson’s correlation coefficient or Spearman coefficient in the case of asymmetrically distributed variables. Techniques of principal component analysis (PCA) will be applied to identify patterns of variables best explaining outcomes of interest.

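### The SUS rates the Companion and game at month 4 but the whole system at month 6, so the planned month 4 to month 6 comparison cannot be read as a change in usability

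*Protocol article*

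**What the plan says.** In the protocol article, Outcomes and variables defines the SUS measurement: "SUS will be applied at month 4 to assess usability of the Companion and the game and at month 6 for the whole system". Table 3 in that section lists the SUS in a single row, marked at months 4 and 6, with no note that the rated object differs. The table's footnote shows that the scale is given to the intervention group only.

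Analysis plan and statistical analysis says that for the intervention group "the results from SUS, EMO, satisfaction, trust and reputation questionnaires will be compared from month 4 to month 6". The same section states in general terms that "the paired t-test will be applied to assess changes within one same group", with nonparametric alternatives where needed.

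Three other sections show what changes between the two ratings. Procedures says "The physical activity monitors are introduced to the participants at the mid-point assessment time at month 4 of the study". Components of the PEGASO platform defines the whole: "The PEGASO system includes physical activity monitoring devices, a web portal, and up to six apps". Focus groups acknowledges the change in exposure for the qualitative work: "Participants in focus groups at month 4 will have only tested the apps and the game of Pegaso", whereas month-6 groups will also have had two months with the sensors.

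**The concern.** A within-person comparison of two scores estimates change over time only if both scores refer to the same thing. Here the object changes at the visit where the second score is taken. A lower month-6 SUS could mean that teenagers tired of the apps, or that the garment and bracelet are harder to use than the software. A higher one could mean growing familiarity, or that the sensors and remaining components are liked. An unchanged score could hide two opposite movements.

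This matters because the Discussion gives the purpose of repeated user-experience measurement as learning how teenagers use such a system over time and passing lessons to developers. Those lessons differ according to which explanation applies, and the SUS comparison as planned cannot tell them apart.

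**Working it through.** The plan gives no figure for this point, so the check sets the sections side by side.

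**Inputs**

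| Item | Month 4 | Month 6 | Section |
|---|---|---|---|
| Object rated by SUS | Companion and game | Whole system | Outcomes and variables |
| Exposure to sensors | Only being introduced | About two months | Procedures; Focus groups |
| SUS in comparison group | No | No | Table 3 footnote |
| SUS scores described per participant | One | One | Outcomes and variables; Table 3 |

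**Step 1: do the two objects really differ?** The narrowest reading of the gap relies on the Companion app section: "The objective of the Companion app is to encompass all other PEGASO apps". If rating the Companion is taken to cover every app, the month-4 object is all the apps plus the game. The monitors and the web portal, both named as parts of the system, are still outside it. The objects differ on either reading.

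**Step 2: what does the planned difference estimate?** Write S(A, t) for the mean SUS of the Companion and game at month t, and S(W, t) for that of the whole system. The planned contrast is

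S(W, 6) − S(A, 4) = [S(W, 6) − S(A, 6)] + [S(A, 6) − S(A, 4)].

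The first bracket is the difference between configurations at month 6. The second is change over time for a fixed object.

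**Step 3: can the brackets be separated?** Both contain S(A, 6), which the article does not describe collecting. The alternative route through S(W, 4) is closed, because participants have not yet used the sensors at month 4. There is one observed difference and two unknowns: if the first bracket is d and the second is −d, the planned contrast is zero for any d. The comparison group has no SUS, so it cannot supply the time trend. Covariate adjustment cannot help either, because every intervention participant changes object at the same visit.

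**Step 4: do the other questionnaires have the same fault?** Table 3 describes the EMO as measuring emotional response to the platform. Outcomes and variables likewise gives the platform as the object of the satisfaction, trust and reputation questionnaire. No change of object between months 4 and 6 is stated for either. The platform gains sensors in between, but the object named stays the same.

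**The case against.** The best defence is that the article hides nothing. It states both SUS objects and says only that the results will be compared. It never calls the contrast a change in a fixed product, and the paired t-test sentence is a general one that does not mention the SUS. A deliberate contrast of partial with full configuration would fit the words. Because the month-6 score is labelled as whole-system, a careful reader would not attribute a fall to the apps alone. Focus groups at both visits and daily usage logs would also help to explain a shift.

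Part of this stands. It is an inference that the authors treat the two scores as repeat ratings of one thing, and a paired test on the SUS is likely rather than stated. The focus groups and logs do help interpretation. But no section describes a partial-versus-full contrast, and Table 3 presents one repeated measure. Even a deliberate contrast of configurations would be mixed with two more months of use. The qualitative and usage data do not supply the missing SUS score.

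A reader might also infer that the EMO, satisfaction, trust and reputation comparisons fail in the same way. The documents do not support that, because the named object is the platform at both visits. The staged introduction of sensors is a reason for care in interpreting those changes, not a mismatch in what is measured.

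**Conclusion.** The point holds for the SUS. A stated analysis does not fit a stated measurement: time and rated configuration are completely confounded in the month 4 to month 6 SUS difference, so it cannot be reported as a change in usability. This follows from the text alone and needs no assumption about variances or sample size.

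Its practical size cannot be given. The documents state neither a standard deviation for the SUS nor an expected difference between the two configurations. A reader might infer that a significant SUS result would be mostly artefact. That is not supported: the documents show that the two sources cannot be separated, not which is larger.

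The reach is limited. One user-experience scale is affected, within the intervention group only, in a study sized mainly to inform a future cluster randomised trial. The comparisons of knowledge, lifestyle and anthropometry between groups are untouched. It is worth correcting because the correction is cheap and the result otherwise has no clear meaning.

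**What to change.** **If month-6 questionnaires can still be changed:** give the SUS twice at month 6, once for the Companion and game with the month-4 wording and once for the whole system. Use only the first in the month 4 to month 6 comparison, and report the second as a separate month-6 estimate. The cost is ten extra items, once, in the intervention group. One limit remains: the sensors feed data into the Companion and the game, so even a like-for-like rating at month 6 is made with the sensors in use. The report should say so.

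**If month-6 data are already collected:** drop the SUS change test and present the two scores descriptively as ratings of two configurations. This may well be the case. Recruitment ran from September to November 2016, and six months from November 2016 is May 2017 if follow-up began promptly, whereas the article is dated December 2019. The cost is wording only.

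**In either case:** add a note to Table 3 that the SUS object differs by visit. For the EMO and the satisfaction, trust and reputation questionnaire, keep the planned comparison and add one sentence saying that sensors were added between the two ratings.

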### Focus groups

Key contributors to understanding the UX of the PEGASO system such as; usability, acceptability, accessibility, context of use, connectedness, desirability and pleasure will also be assessed through focus groups; moreover they will be used to gain insight on users understanding of the system and their experience and motivation to engage/disengage with the PEGASO system and its different component parts (apps, games and sensors). Participants in the focus groups will be recruited from participants in the intervention group. A total of four focus groups per participating site (England, Lombardy and Catalonia) will be undertaken at month 4 and 6. Participants in focus groups at month 4 will have only tested the apps and the game of Pegaso, whilst participants on the Month 6 focus groups additionally will have used the sensors for 2 months. Each focus group will consist of 4–8 participants. The groups, whenever possible, will be gender-balanced with different levels of engagement to the PEGASO system. A trained moderator will guide the focus group following a script and will be assisted by an observer. All of them will be audio and/or videotaped and transcribed systematically, literally, and anonymously. An analysis will be made of thematic content, coding the data and grouping them into predefined categories based on topics.

### Anthropometric variables

Anthropometric variables are assessed at baseline and at the end of the intervention as secondary outcomes. Body weight and percentage of body fat is assessed by bioelectric impedance analysis (BIA) performed using a homologated electronic scale (Tanita sc-240 ma) with the participant wearing light clothing and no shoes. Height is also measured with a portable system with the participant shoeless in the standing position (SECA 213). Body mass index (BMI) is calculated as weight (kg) divided by height squared (m2). Waist circumference is measured using a flexible graduated measuring tape (SECA 201) with the patient in the standing position without clothing covering the midsection of the torso. All the anthropometric measurements are undertaken in the most private way possible.

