## Background

Adolescence is a period characterised by significant changes at physical and psychological levels [1]. It is a life-course stage vulnerable to acquiring unhealthy behaviours such as insufficient levels of physical activity and excess of sedentary behaviour, poor diet and sleep deprivation [2]. Several studies highlight the importance of adopting and maintaining healthy lifestyles amongst young people to ensure physical health and mental wellbeing during adolescence and adulthood [3–6]. Interventions that facilitate healthy dietary habits [7]; regular physical activity [8]; adequate sleep duration [9], and reduced sedentary behaviour [10, 11] were shown to be effective in preventing and treating obesity and other risk factors of non-communicable conditions such as type II diabetes, cardiovascular disease or cancer. However, available evidence is still overall considered to be of low to moderate quality [12, 13].

In Europe the proportion of overweight individuals in the general population is a relevant public health problem. According to the World Health Organization (WHO), the prevalence of overweight (body mass index >85th percentile) among European 13-year-olds is 27% [6, 14]. Overweight during childhood and adolescence is a risk factor for obesity in adulthood [15] and thus overweight control by empowering healthy lifestyles habits among adolescents is generally considered a fruitful strategy of public health promotion. Several social, school-based and media campaigns have been conducted aiming to motivate behaviour change [12]. However, in children and adolescents, evidence of a reduction in overweight and obesity prevalence is lacking [16] and the prevalence of related unhealthy behaviour is still very high [17]. This suggests that innovative intervention strategies, more engaging and attractive for children and adolescents, are needed.

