### Participant selection criteria

Eligible for inclusion in this study were teenagers aged 13 to 16 years (inclusive) without physical or psychological conditions that would prevent the understanding of and their participation in the intervention, who were able to participate in the study for 6 months and had an adequate proficiency in the local language (Italian, Catalan/Spanish and English). Although it is generally accepted that adolescence extends beyond this age, range 13–16 years was chosen as the most feasible age range to introduce this type of intervention in a school context.

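### Within-group pre/post tests of unstandardised BMI in growing 13–16-year-olds cannot separate effect from growth; the between-group contrast leaves out age, and the text and Table 3 disagree on the body-composition analyser

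*Protocol article*

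**What the plan says.** **Population.** The section on participant selection criteria admits "teenagers aged 13 to 16 years (inclusive". The section on recruitment and group allocation describes whole classes, or first-responding volunteers, with controls from the same or another school. There is no randomisation.

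**Measure.** The section on anthropometric variables states "Anthropometric variables are assessed at baseline and at the end of the intervention as secondary outcomes", and "Body mass index (BMI) is calculated as weight (kg) divided by height squared (m2". Table 3 lists height, waist, weight, BMI, % body fat and % body water at baseline and month 6. No age- and sex-standardised version is named. The only age-relative measure is in the Background, where prevalence is quoted for "overweight (body mass index >85th percentile".

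**Analysis.** The abstract lists both between- and within-group changes for outcomes that include anthropometry. The analysis section states "Knowledge/awareness, lifestyles and anthropometric measurements will be compared at pre and post intervention (month 6" and assigns the paired t-test to change within one group. It then says that the intervention effect is analysed by comparing the changes in the two groups, with Cohen d and adjustment for influential variables. The factors it names for control are gender, cultural and socioeconomic level, BMI and baseline lifestyles. Age is collected in the on-line questionnaires but is not on that list.

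**Analyser.** The text on anthropometric variables says that impedance analysis is "performed using a homologated electronic scale (Tanita sc-240 ma", with no site exception. Table 3 gives that model for England, Catalonia and Italy, and for Scotland the "Tanita MC780MA Multi" frequency segmental analyser.

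**The concern.** At 13 to 16, weight, waist and BMI are expected to rise with normal growth, at a pace that depends on age and sex. A paired test of kg/m² asks whether BMI moved at all, and growth alone can answer yes. A significant rise in the intervention group could be read as harm. A smaller rise than feared could be read as benefit. Neither reading would be sound.

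The concurrent comparison group protects the between-group contrast only to the extent that the two groups grow alike. When classes or volunteers form the groups, and some controls come from another school, the age mix may differ between them.

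The two analysers raise a separate question: whether a body-composition figure from Scotland is on the same scale as one from the other three sites. The analysis section plans baseline comparisons by site, and there analyser and site cannot be separated.

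**Working it through.** The article states no growth rate, SD of change or analyser offset, so there is no anthropometric figure of its own to reproduce. Its sample-size section gives 525 at 2:1, which splits into 525 × 2/3 = 350 intervention and 525 × 1/3 = 175 comparison pupils. Alpha is 0.05, two-sided. Everything else below is an assumption, shown as a range. All calculations use the normal approximation, assume no intervention effect, and ignore clustering and dropout.

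**1. Within-group test.** With mean growth g and SD of change s, SE = s/√n, and the rejection rate is Φ(g/SE − 1.96) + Φ(−g/SE − 1.96).

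Example: g = 0.1, s = 0.8, n = 350. SE = 0.8/18.71 = 0.0428 and g/SE = 2.34, so the rate is Φ(0.38) ≈ 65%.

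| Growth alone (kg/m²) | Intervention group, n = 350 (s = 1.5 to 0.8) | Comparison group, n = 175 (s = 1.5 to 0.8) |
|---|---|---|
| 0.1 | 24–65% | 14–38% |
| 0.2 | 70–99.7% | 42–91% |
| 0.3 | 96–100% | 75–100% |

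The larger group is also more likely to show a significant change from the same growth, purely because of its size. One group significant and the other not would therefore be no evidence of an effect.

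**2. Between-group comparison of changes.** SE = s × √(1/350 + 1/175) = 0.0926 × s. With equal growth in both groups the expected difference is zero and the rejection rate is 5%. With a growth difference D, the rate is Φ(D/SE − 1.96) + Φ(−D/SE − 1.96).

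Example: D = 0.1, s = 0.8. SE = 0.0741 and D/SE = 1.35, so the rate is Φ(−0.61) ≈ 27%.

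| Growth difference D (kg/m²) | False-positive rate (s = 1.5 to 0.8) | Spurious Cohen d (D/s) |
|---|---|---|
| 0 | 5% | 0 |
| 0.02 | 5.2–5.8% | 0.01–0.03 |
| 0.05 | 6.5–10% | 0.03–0.06 |
| 0.1 | 11–27% | 0.07–0.13 |

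For scale, a difference of 0.1 is one third of an assumed total growth of 0.3. It needs a clear imbalance between the groups.

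**3. Analyser.** If an analyser reads b points too high and the same one is used at both visits, a pupil's change is (Y6 + b) − (Y0 + b) = Y6 − Y0, and b cancels. In pooled levels, the group difference shifts by b × (Scottish share in intervention − Scottish share in comparison). With an assumed b = 2 points and shares of 30% and 20%, the shift is 2 × 0.10 = 0.2 points. With equal shares it is 0. In a comparison of Scotland with the other sites at baseline, the whole of b enters.

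**The case against.** The strongest reply is that the article does not rest its effect estimate on the within-group test. It compares change with change, so growth common to both groups drops out. That stands. A reader might infer from the raw BMI definition that growth is mixed into the anthropometric results generally, or that the near-certain rejection rates in step 1 are the trial's false-positive rate. The documents support neither reading. Those rates concern the paired test only and depend on assumed inputs.

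A second reply is that the formula for BMI is also the first step towards any z-score, and that a condensed article may leave standardisation to a fuller plan. Likewise, BMI as a control factor is not said to be raw, and adjustment for influential variables does not exclude age. This is fair, and no contradiction with the percentile in the Background is claimed, since that percentile defines a prevalence and not an outcome. What remains is what the text does state: within-group change in anthropometry is a planned result tested by paired t-test, and the list of named control factors includes gender but not age.

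Third, a reader might infer that the second analyser distorts the body-fat results as a whole. Analysers are assigned by site and not by arm, so a constant offset cancels in each pupil's change. The offset matters for levels, and the conflict between the text and Table 3 remains. The table's layout is broken in the copy reviewed, so it is uncertain exactly which rows the second analyser covers.

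Finally, the stakes are modest: these are secondary outcomes in a study meant largely to test feasibility and inform a later trial.

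**Conclusion.** The point holds in three limited parts.

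- **Within-group tests of anthropometry are uninformative about the intervention.** This follows from the design. Only the size depends on assumptions: 24–65% rejection in the intervention group for growth of 0.1 kg/m², and 96–100% for 0.3.
- **The between-group change is open to bias only from unequal growth.** That is possible because allocation is not randomised and age is not a named control factor. For a 0.1 kg/m² difference and an SD of change of 0.8–1.5, false positives are about 11–27%. For 0.05 they are 6.5–10%, and for equal growth 5%. The documents do not show that such a difference exists.
- **The analyser description contradicts itself.** A constant offset does not bias change if each site keeps its analyser throughout. It does confound absolute comparisons between Scotland and the other sites, and its size is unknown.

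**What to change.** - Analyse BMI as an age- and sex-standardised z-score from one named growth reference. At minimum, adjust the anthropometric change models for baseline age, sex and site.
- State that conclusions on anthropometry rest on the between-group difference in change, and report within-group changes as description without a claim of effect.
- Reconcile the section on anthropometric variables with Table 3 on which analyser each site uses and for which measures.
- Analyse % body fat and % body water as within-person change with a site term, and do not interpret absolute differences between Scotland and the other sites at baseline.

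The cost is wording and analysis code only, since age, gender, height and weight are already collected. Z-scores are less intuitive, so raw means can stay in the tables as description. Changing the waist measure to a waist-to-height ratio, or barring any test of raw weight, would be a matter of preference and is not needed here.
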